## Data Management and Statistical Analysis Plan

All data will be systematically coded and double-entered into a data system stored on a secure server according to institutional, state, and federal policies. Contact information was obtained from electronic health records and stored on a secure, password-protected server with access limited to study staff and will be destroyed after 5 years as required.

A detailed statistical analysis plan, finalized prior to enrolling the first patient, is available from the authors upon request; here, we provide key elements of that plan for analysing the co-primary outcomes. The biostatistician and principal investigators are blinded to treatment assignments, but the study field staff are not blinded. For primary analyses, all randomized patients will be analysed according to their randomized group regardless of the extent to which they performed SMBG (intention-to-treat). Missing 52-week outcome data will be ignored for the primary analyses. First, we will compare change in A1c from baseline through 52 weeks across the three randomization groups using an analysis of covariance (ANCOVA) conducted at the 0.05 significance level. This ANCOVA model will control for baseline A1c, prior use of SMBG, duration of T2DM, baseline anti-hyperglycemic treatment, age, race/ethnicity, health literacy, and number of baseline comorbidities. If the overall null hypothesis of no difference between the three groups is rejected, we will compare each SMBG group to the no testing group separately using the Dunnett-Tamhane Step-Up procedure for multiple comparisons to control the family-wise error rate at 0.05 (69). We will also conduct a contrast test comparing the average of the two SMBG groups to the no testing group at the 0.05 level. Similar ANCOVA models will compare change in SF-36 physical and mental component scores between groups, controlling for the same baseline variables as for A1c. Because we are examining two aspects of HRQOL, we will apply a Bonferroni correction and assess each comparison at the 0.025 level. We will not adjust for multiple comparisons due to the co-primary endpoints of A1c and HRQOL. In addition, we will assess for potential effect modification for each of the baseline variables included in the models by adding appropriate interaction terms to the ANCOVA model one at a time. Each interaction term will be tested separately at the 0.05 significance level. Only if the associated interaction term is significant, similar contrasts to those described above will be assessed within the relevant subgroups. Similar ANCOVA methods will be used to compare groups on each of the secondary outcomes. These tests will each be conducted at the 0.05 significance level with no adjustments for multiple comparisons.

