**Methods/Design:**

Using stakeholder engagement approach, we developed and implemented a pragmatic trial of patient with non-insulin treated T2DM patients from five primary care practices randomized to one of three SMBG regimens: 1) no testing; 2) once daily testing with standard feedback consisting of glucose values being immediately reported to the patient through the glucose meter; and 3) once daily testing with enhanced patient feedback consisting of glucose values being immediately reported to the patient PLUS automated, tailored feedback messaging delivered to the patient through the glucose meter following each testing. Main outcomes assessed at 52 weeks include quality of life and glycemic control.

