**Discussion:**

This pragmatic trial seeks to better understand the value of SMBG in non-insulin treated patients with T2DM. This paper outlines the protocol used to implement this study in fifteen community-based primary care practices and highlights the impact of stakeholder involvement from the earliest stages of project conception and implementation. Plans for stakeholder involvement for result dissemination are also discussed.

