#### Randomization

After providing informed consent, baseline A1c, and completing the baseline study interview, participants will be randomized to one of the three treatment arms using sequentially numbered, opaque, sealed envelopes. The allocation sequence is generated using computer-generated randomly permuted blocks of random sizes. The randomization is stratified by study practice. The Field Coordinator reviews the treatment assignment with the patient, using a standardized script, provide the initial training and supplies necessary for participation in the study and answer any remaining questions (Fig. 1).

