##### Qualitative Assessment of Patient Outcomes

Individual phone interviews will be conducted by researchers skilled in qualitative data collection. At each participating practice, we will interview approximately 6 patients who have completed the study. Two patient participants from each arm will be recruited for each of the 13 practices (*N* = 78 patients). Every effort will be made to recruit a range of high and low engagement for testing arms. Interviews will last approximately 30–45 min and will include these topics: impressions of and experience with SMBG prior to and during the trial, including using a wireless glucometer and messaging system, and impressions of using the downloaded SMBG reports at clinic visits, interactions with providers about diabetes care before and during the study, and strategies for dissemination and communication. All participants will review, sign, and be given a copy of the IRB-approved informed consent document specific to the focus groups.

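### Practice, the factor that stratifies randomisation, is missing from the stated ANCOVA models; if practice is prognostic, the tests are mildly conservative

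*Protocol article*

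**What the plan says.** - **Design.** Under Randomization, the protocol article states: "The randomization is stratified by study practice". It adds: "The allocation sequence is generated using computer-generated randomly permuted blocks of random sizes".
- **A1c model.** Under Data Management and Statistical Analysis Plan: "This ANCOVA model will control for baseline A1c, prior use of SMBG, duration of T2DM, baseline anti-hyperglycemic treatment, age, race/ethnicity, health literacy"; the count of baseline comorbidities is the eighth and last variable. Practice is not listed.
- **SF-36 models.** Both component scores are analysed "controlling for the same baseline variables as for A1c", so practice is absent there too.
- **Secondary outcomes.** They are to be analysed by similar ANCOVA methods. The omission there is an inference, not an explicit statement.
- **Number of strata.** The abstract's methods paragraph has "five primary care practices", its discussion paragraph "fifteen community-based primary care practices", and the qualitative section "each of the 13 practices". The last agrees with that section's own total: 13 practices × 6 patients = 78.

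The article mentions no fixed or random practice effect anywhere.

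**The concern.** Permuted blocks within practice make the arms nearly equal in their mix of practices, so differences between practices largely cancel from the arm comparison. An analysis that ignores practice does not use this. It estimates the residual variance as if between-practice variation still added noise to the comparison, so the reported standard error exceeds the true one.

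Tests of both co-primary outcomes would then reject less often than their nominal level under the null, confidence intervals would be wider than needed, and some power would be lost. The error is in the cautious direction. It matters because the stratum is already recorded and using it costs almost nothing.

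**Working it through.** **Inputs from the article (Sample Size).** 150 randomised per arm; 10% loss, so 135 evaluable per arm and 405 in all; A1c difference d = 0.325%; SD of change 0.8%, or 1.0% as the pessimistic case; level 0.05 for A1c and 0.025 for each SF-36 component.

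**Input that must be assumed.** r, the share of residual variance lying between practices after the listed covariates. I show 0.02, 0.05 and 0.10. The stated SDs are used as the residual SD of the model without practice.

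**Step 1: the plan's own power.** Both testing arms are taken to be shifted by 0.325% from no testing.

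| Comparison | SD 0.8% | SD 1.0% |
|---|---|---|
| Overall three-group F test | 94.0% | 79.1% |
| Both testing arms vs no testing | 97.1% | 86.9% |
| One testing arm vs no testing | 91.6% | 76.1% |

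The claim of at least 90% at SD 0.8% reproduces. The claim of at least 80% at SD 1.0% holds for the pooled contrast, is missed by about a point for the overall test, and is not met for a single pair.

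**Step 2: standard error and size.** With balance within practice, the true variance of the arm difference is proportional to 1 − r, while the model without practice uses about 1.

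- Inflation of the standard error: 1/√(1 − r).
- Size of a single two-sided contrast: 2[1 − Φ(z/√(1 − r))], with z = 1.960 at level 0.05 and 2.241 at level 0.025.
- Size of the overall test (2 df, large sample): 0.05^(1/(1 − r)). At r = 0.05 this is 0.05^(1/0.95) = 0.043.

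| r | SE factor | Overall test, 0.05 | Contrast, 0.05 | Contrast, 0.025 |
|---|---|---|---|---|
| 0 | 1.000 | 0.050 | 0.050 | 0.025 |
| 0.02 | 1.010 | 0.047 | 0.048 | 0.024 |
| 0.05 | 1.026 | 0.043 | 0.044 | 0.021 |
| 0.10 | 1.054 | 0.036 | 0.039 | 0.018 |

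**Step 3: power of a single pair.** Let SE = SD·√(2/135), so d/SE is 3.338 at SD 0.8% and 2.670 at SD 1.0%. Power without practice is Φ((d/SE − 1.96)/√(1 − r)); with practice it is Φ(d/(SE·√(1 − r)) − 1.96).

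| r | SD 0.8%: without → with | SD 1.0%: without → with |
|---|---|---|
| 0.02 | 91.8% → 92.1% | 76.3% → 77.0% |
| 0.05 | 92.1% → 92.8% | 76.7% → 78.2% |
| 0.10 | 92.7% → 94.0% | 77.3% → 80.4% |

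**Step 4: the loss in patients.** Equating the two powers, the adjusted model needs only m = 135·[1 − 1.96(1 − √(1 − r))/(d/SE)]² evaluable patients per arm. At r = 0.05 and SD 1.0%: 1.96 × 0.0253/2.670 = 0.0186, so m = 135 × 0.9814² = 130.0. The saving is about 5.0 per arm, and 5.0 × 3/0.9 is about 17 randomised patients. For r = 0.02, 0.05 and 0.10 the saving is 5, 13 and 27 at SD 0.8%, and 7, 17 and 33 at SD 1.0%.

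**Step 5: simulation.** Stratified permuted blocks (sizes 3 and 6 assumed), 405 patients, no other covariates. Omitting practice gave an overall-test size of 0.042 at r = 0.05 with both 5 and 15 practices, and 0.038 (5 practices) or 0.044 (15) at r = 0.10. The ratio of model-based to empirical standard error was 1.02 to 1.03 and 1.04 to 1.05. With practice included, the size was 0.048 at r = 0.05 for both counts, and 0.050 (5) or 0.057 (15) at r = 0.10. The 0.057 came from 6,000 runs and lies about 2.5 simulation standard errors above 0.05. At r of 0.02 or less the effect could not be told from simulation error.

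**The case against.** **The effect is conditional. This stands.** A reader might infer that the trial's p-values and intervals are simply wrong. The article does not support that: it reports no practice-level variance, and at r = 0 the omission has no effect. The outcome is change in A1c adjusted for baseline, which already removes much of any difference in level between practices.

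**The mechanism is uncertain. This stands in part.** It is tempting to say that practices differ in how providers act on glucose reports. The article does not say so, and only the two testing arms generate such reports, so that variation would mainly be a varying treatment effect rather than the common practice effect behind the standard-error argument. All providers are also guided by the same ADA guidelines. On the other side, the discussion and its Table 4 record that testing advice and testing itself vary in practice, and the eight covariates all describe the patient.

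**The loss is easy to overstate. This stands.** A reader might multiply 450 by r and report 9, 22 or 45 patients lost. That figure describes interval width. Under balance the unadjusted difference already has the smaller variance and only its estimated standard error is too large, so the power loss is smaller, as in Step 4. At the design SD of 0.8% power is ample either way.

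**The article is a condensation. This does not remove the point.** It gives key elements of a fuller plan that might include practice. But it lists the covariates one by one; if the full plan adds practice, the published model is misdescribed.

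**Adding practice has a side effect. This stands.** The plan tests effect modification for every baseline variable in the model. Read literally, practice would bring an interaction test with up to (15 − 1) × (3 − 1) = 28 degrees of freedom and, if significant, contrasts within practices averaging 405/15 = 27 evaluable patients.

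**Conclusion.** The stated A1c and SF-36 models omit the randomisation stratum, and the secondary models appear to do the same. If practice is prognostic after the listed covariates, the tests are mildly conservative. Over r = 0.02 to 0.10 the size of the overall A1c test falls to between 0.047 and 0.036, intervals are about 1% to 5.4% too wide, and the power loss is worth 5 to 27 randomised patients at SD 0.8% or 7 to 33 at SD 1.0%. These figures rest on the assumed r, near-balance within practice and normal approximations.

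This is a matter of efficiency, not validity: type I error is not inflated, no estimate is biased, and a positive result would not be called into question. The conflict over five, 13 or fifteen practices is real, but it bears only on how the strata are defined. It does not make the omission more serious. The change is worth making because it is nearly free.

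**What to change.** 1. Before unblinding, add study practice, as used in the randomisation list, to the A1c, SF-36 and secondary ANCOVAs as a fixed or random effect. Set a rule in advance for pooling very small practices.
2. State that practice is a design covariate and is excluded from the effect-modification tests and the subgroup contrasts that follow them.
3. Reconcile the number of practices across the abstract and the qualitative section with the randomisation list.
4. If the full analysis plan already includes practice, correct the article's description of the model instead.

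**Cost.** As a fixed effect, one factor using at most 14 of roughly 400 residual degrees of freedom. The article says the full plan was finalised before the first enrolment and that all 450 patients are recruited, so this needs a dated amendment. The biostatistician and principal investigators are described as blinded, so it can still be made without knowledge of the results. No new data are needed.

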#### Measures

The two primary outcomes of the study are change in A1c and change in health related quality of life (HRQOL). The A1c was chosen due to its use in prior studies and its standing as a measure on which: 1) providers evaluate patients; 2) payers evaluate providers; and 3) patients evaluate themselves and their providers [2]. Though HRQOL is also critically important to patients, few studies have rigorously examined the impact of SMBG on HRQOL. Based on these facts and the recommendations of our stakeholder groups, HRQOL is a co-primary outcome for this pragmatic trial. We will utilize the Short Form 36 (SF-36) to assess overall quality of life. We will use the physical component score (PCS) and the mental component score (MCS), with scores standardized to a normal distribution (mean = 50 and standard deviation[SD] = 10) [16]. It has been widely used and validated in medical studies generally and diabetes studies in particular [17–20]. All primary and secondary outcomes are outlined in Table 2. Because the 52-week time point may not align with a scheduled primary care visit, we have defined this time point as 52 ± 6 weeks from the baseline visit.

**Table 2 Tab2:** Primary and secondary patient-centered outcomes

	Clinical Outcomes	Time	Patient Reported Outcomes	Time
Primary	Glycemic control (A1c)	Baseline/52 weeks	Quality of life (QOL)	Baseline/52 weeks
Secondary	Hypoglycemia frequency	Baseline/52 weeks	DM-related QOL	Baseline/52 weeks
	Health care utilization	Baseline/52 weeks	DM self-care	Baseline/52 weeks
	Treatment regimen modification	Baseline/52 weeks	DM treatment satisfaction	Baseline/52 weeks
			DM-related self-efficacy	Baseline/52 weeks
			Patient-provider communication	Baseline/52 weeks

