## Sample Size

We desire high power for our primary between-arm comparison as well as reasonable power to detect an important effect modifier, should one exist. In a recent Cochrane Review, the estimated mean 12-month differences between SMBG and control groups were−0.13 and−0.52%, respectively, for patients diagnosed more than and less than 1 year prior to the study [1]. Assuming approximately equal enrollment of newly diagnosed and long term patients, this implies a mean difference of−0.325%. Based on results from one of the larger and better quality trials conducted to date, we assume the standard deviation for ΔA1c would be 0.8% [4]. We assume no more than 10% loss to follow-up. Given these assumptions, randomizing 150 patients per group would provide at least 90% power for the primary comparison for A1c at the 0.05 significance level. This same sample size would provide at least 80% power for the primary comparison if the true standard deviation were as high as 1.0%. For comparing mean change in HRQOL between groups, we will use the physical and mental component scores of the SF-36, both of which range from 0 to 100. Because we are interested in two different aspects of QOL, we will apply a Bonferroni correction and assess each comparison at the 0.025 level. Based on observed results from the ZODIAC-17 SMBG study, we conservatively assume that the standard deviation for the change scores for either component will be 10 points [2]. Under these assumptions, randomizing 150 patients per group with no more than 10% loss will provide at least 80% power to detect an overall difference between groups if the mean difference between the highest and lowest groups is at least 4 points.

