If yes, how often told: a few times a month				14 (4.2)	
If yes, how often told: once a month				2 (0.6)	
If yes, how often told: < once a month				1 (1.2)	
If yes, how often didn’t know				77 (22.9)	
If Testing = No, ever tested?				78 (69.6)	
If yes, at least daily				55 (70.5)	
If yes, not daily, but > 1X/week				10 (12.8)	
If yes, a few times a month				3 (3.9)	
If yes, once a month				1 (1.3)	
If yes, less than once a month				9 (11.5)	
If yes, how long did you test: <= 1 month				8 (10.3)	
If yes, how long did you test: <1 year >1X/month				35 (44.9)	
If yes, how long did you test: 1 year				12 (15.4)	
If yes, how long did you test: > 1 year < 5 years				17 (21.8)	
If yes, how long did you test: > = 5 years				6 (7.7)	
# Testing = No, why not?				112 (24.9)	
Not told to test				50 (44.6)	
Costs				18 (16.1)	
Pain				8 (7.1)	
Disruptive				4 (3.6)	
Does not understand why should test				7 (6.25)	
Constant reminder of DM				10 (8.9)	
Other reason				30 (26.8)	
Medications and BMI					
# of prescription medications	6.2 (3.4)	0	17		
# of DM medications	1.4 (0.9)	0	5		
BMI (max weighs 523 lb)	34.3 (7.7)	20.8	75.0		
Primary Endpoints					
Hemoglobin A1c (%)	7.6 (1.1)	5.7	13.1		
SF36—Physical Health	47.4 (8.9)	10.4	63.0		
SF36—Mental Health	53.3 (9.2)	9.5	68.0		
Secondary Endpoints^a^					
Diabetes Empowerment Scale—Short Form	4.3 (0.5)	1.1	5		1
Diabetes Symptom Checklist—Revised	20.4 (21.4)	0	107.2		
Diabetes Treatment Satisfaction—satisfaction	31.8 (5.1)	6	36		6
Diabetes Treatment Satisfaction—perceived control	2.7 (2.6)	6	12		23
Problem Areas in Diabetes	13.1 (16.2)	0	82.5		
Summary of Diabetes Self-Care Activities (SDSCA) (# of days in last 7)					
General Diet	4.3 (2.2)	0	7		1
Special Diet	4.1 (1.8)	0	7		
Carb spacing	4.1 (2.4)	0	7		
Exercise	2.9 (2.2)	0	7		
Blood glucose testing (only # times tested)	2.6 (2.8)	0	7		1
Foot care	3.2 (2.5)	0	7		
Communication Assessment Tool—MD items	4.5 (0.7)	1.5	5		1
Communication Assessment Tool—staff item	4.6 (0.7)	1	5		
Health Literacy					
Newest Vital Sign	3.8 (2.0)	0	6		2
Newest Vital Sign (% >4 = literate) (median = 4)				235 (61.8)	2

^a^Min/max may contain a decimal if missing data within the allowable limit were present

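### The models for the co-primary SF-36 component scores are given the A1c covariate list, which includes baseline A1c but not the component's own baseline; adding it would be a nearly free gain in precision

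*Protocol article*

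**What the plan says.** The Data Management and Statistical Analysis Plan section of the protocol article first sets out the A1c model: "This ANCOVA model will control for baseline A1c, prior use of SMBG, duration of T2DM, baseline anti-hyperglycemic treatment, age, race/ethnicity, health literacy". A count of comorbid conditions completes the list. That makes eight covariates. One is the outcome's own baseline value, and none is a quality-of-life score. The section then turns to quality of life: "Similar ANCOVA models will compare change in SF-36 physical and mental component scores between groups, controlling for the same baseline variables as for A1c".

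The Measures section gives this outcome full standing: "HRQOL is a co-primary outcome for this pragmatic trial". Table 3, under Baseline Statistics, reports baseline values for both components, with SDs of 8.9 for PCS (the row "SF36—Physical Health") and 9.2 for MCS, and lists no missing values for either. No other part of the article adds baseline PCS or MCS to the models.

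The Sample Size section plans the quality-of-life comparison on the raw change score: "we conservatively assume that the standard deviation for the change scores for either component will be 10 points".

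**The concern.** The plan adjusts A1c change for baseline A1c but, on its wording, does not give the other co-primary outcome the same treatment. Baseline A1c has no obvious claim to explain change in PCS or MCS, whereas a score's own baseline is usually the strongest predictor of its change, because high starters tend to fall and low starters tend to rise.

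Two things are at stake. The first is precision: a change score not adjusted for its baseline has a larger residual variance than one that is. The second is protection against chance imbalance: if one arm happens to start higher, part of that difference appears in the change contrast. Both bear on endpoints that are each tested at the stricter level: "we will apply a Bonferroni correction and assess each comparison at the 0.025 level".

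**Working it through.** **Inputs.** From Sample Size: change SD 10, 150 randomised per group, at most 10% loss (150 × 0.9 = 135 evaluable), level 0.025 per component, and a target stated as "if the mean difference between the highest and lowest groups is at least 4 points". From Table 3: baseline SD s = 8.9 (PCS) and 9.2 (MCS). Assumed: the same SD at baseline and at 52 weeks, and a correlation rho between the two, which the documents do not give.

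**The plan's own power figure.** The plan claims at least 80%. I used a three-group overall F test with 135 per group, SD 10 and level 0.025. With means 0, 2 and 4 the noncentrality is 135 × (4 + 0 + 4)/100 = 10.8, and power is 76.6%. With two groups equal and the third 4 points away, it is 88.9%. The first pattern is the least favourable for a 4-point range and serves as the reference below.

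**Variance with and without the baseline.**
- Change score, unadjusted for baseline: 2s²(1 − rho).
- Adjusted for baseline: s²(1 − rho²).
- Ratio: (1 + rho)/2, so the reduction is (1 − rho)/2.

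**Correlation implied by the planning SD.** rho = 1 − 10²/(2s²).
- PCS: 1 − 100/158.42 = 0.37. Reduction 31.6%; residual SD 10 × √0.684 = 8.27.
- MCS: 1 − 100/169.28 = 0.41. Reduction 29.5%; residual SD 10 × √0.705 = 8.39.

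**Power across the range** (means 0/2/4, 135 per group, level 0.025). For rho of 0.5 and above, the Table 3 SDs are kept, so the change SD itself falls as rho rises.

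| Component, rho | Change SD | Adjusted SD | Variance cut | Power without → with baseline |
|---|---|---|---|---|
| PCS, 0.37 | 10.0 | 8.27 | 32% | 76.6% → 91.8% |
| PCS, 0.5 | 8.90 | 7.71 | 25% | 87% → 95% |
| PCS, 0.6 | 7.96 | 7.12 | 20% | 94% → 98% |
| PCS, 0.7 | 6.89 | 6.36 | 15% | 98.5% → 99.5% |
| MCS, 0.41 | 10.0 | 8.39 | 30% | 76.6% → 90.9% |
| MCS, 0.5 | 9.20 | 7.97 | 25% | 84% → 94% |
| MCS, 0.7 | 7.13 | 6.57 | 15% | 98% → 99% |

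**Chance imbalance.** The standard error of a two-arm difference in baseline PCS is 8.9 × √(2/135) = 1.08 points. A baseline difference d moves the unadjusted change contrast by (1 − rho)d, not by d. For a one-standard-error imbalance this is 0.63 × 1.08 = 0.7 points at rho 0.37, and 0.3 × 1.08 = 0.3 points at rho 0.7, against a 4-point target.

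**The other covariates.** The formulas ignore the seven other listed covariates besides baseline A1c. If these explained an equal share, 10-30%, of both the baseline and the 52-week scores, the reduction at rho 0.6 would be 22-29% instead of 20%.

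**The case against.** The article presents only key elements of a detailed plan that is not shown. Its A1c model is the outcome's own baseline plus seven general covariates, so the quality-of-life sentence may be shorthand for the same structure with the baseline swapped. Authors who adjust A1c for its baseline clearly know the practice. This is a fair reading of the intention, and the article cannot settle it. But the sentence names the covariates as the same ones, so the literal reading is the stronger, and the wording needs correcting either way.

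The harm is also limited. Under randomisation the change-score comparison is unbiased, and regression to the mean acts equally in all arms in expectation. The sample size used the raw change SD, so the design and the stated analysis agree and adjustment would be a bonus. The plan calls its SD of 10 conservative; if the true SD is smaller, rho is higher, unadjusted power is already good, and the gain shrinks. All of this stands.

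A reader might infer three stronger things that the documents do not support:
- **That the planned quality-of-life power fails because of this omission.** The 76.6% is a separate matter that depends on the pattern of means, and the power calculation never assumed baseline adjustment.
- **That the full 1.1-point baseline imbalance carries into the estimate.** Only the fraction (1 − rho) does.
- **That the secondary scales have the same fault.** For those the text promises similar methods without fixing the covariates, which is ordinary detail for the full analysis plan.

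**Conclusion.** The point holds as a free efficiency improvement on a co-primary outcome. It does not threaten validity and does not have to be fixed for the trial to stand. As written, the PCS and MCS models adjust for baseline A1c and not for the baseline of the score they analyse.

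The residual variance given up is about 30-32% if the planning SD of 10 is right, and 25-15% if the correlation is 0.5-0.7. The gain in power is about 14-15 points in the first case, which is the most favourable one, and about 1-10 points in the second. These sizes rest on an assumed correlation, equal SDs at both times, 135 evaluable patients per group and the 0/2/4 pattern of means. That adjustment gains precision holds throughout the range shown; how much it gains cannot be fixed from the documents.

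**What to change.** Before unblinding, amend the quality-of-life sentence in the analysis section to say that the PCS change model includes baseline PCS and the MCS change model includes baseline MCS, each in addition to the covariates already listed. If the full analysis plan already says this, only the article's wording needs correcting.

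The cost is one sentence and one degree of freedom per model. No new data are needed, since both scores were collected at baseline. The timing matters because a covariate added to a co-primary model after unblinding could look data-driven.

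### The fixed 0.025 split between the two SF-36 component scores is valid but needlessly conservative: Holm on the two overall tests keeps their error at 0.05 and gains power when both components are affected

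*Protocol article*

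**What the plan says.** The Protocol article fixes the rule twice. The Data Management and Statistical Analysis Plan section states: "Because we are examining two aspects of HRQOL, we will apply a Bonferroni correction and assess each comparison at the 0.025 level". The Sample Size section matches it: "Because we are interested in two different aspects of QOL, we will apply a Bonferroni correction and assess each comparison at the 0.025 level". Neither section provides a step-down, so each component keeps 0.025 whatever the other shows.

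The tests concerned are the overall comparisons of the three arms: "Similar ANCOVA models will compare change in SF-36 physical and mental component scores between groups". For A1c, the same section follows a significant overall test with step-up comparisons of each SMBG arm against no testing, plus a contrast of the two SMBG arms together against no testing. The SF-36 models are called similar, so the same follow-ups presumably apply to them, though the article does not say so outright. It makes no adjustment between A1c and HRQOL.

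The article does not say whether an HRQOL effect must be shown on one component or on both, and it gives no PCS–MCS correlation.

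**The concern.** With two hypotheses, Holm tests the smaller p-value at 0.025 and, only if that is significant, the larger at 0.05. Suppose PCS has an overall p of 0.001 and MCS one of 0.03. The plan reports an effect on PCS only, whereas Holm reports both. For these two overall tests the stricter rule buys no extra familywise protection.

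HRQOL is a co-primary outcome, and the article treats physical and mental health as two separate aspects. Which of them changes is therefore part of the question. At stake is a true effect on both components being reported more often than necessary as an effect on one.

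**Working it through.** **Inputs** (Sample Size section unless noted)
- 150 per arm with at most 10% loss: 150 × 0.90 = 135 analysed per arm. Missing outcomes are ignored under the analysis section.
- SD of change: "we conservatively assume that the standard deviation for the change scores for either component will be 10 points".
- Effect: "if the mean difference between the highest and lowest groups is at least 4 points". The middle arm's position is not given, so two patterns are shown: 0/2/4 (midpoint) and 0/4/4 (middle arm equal to an extreme).
- Levels: 0.025 under the plan, and 0.05 for the second Holm step.
- PCS–MCS correlation ρ: not given. It is assumed and varied from −0.3 to 0.9.

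**Step 1. The plan's own power figure.** The article states: "randomizing 150 patients per group with no more than 10% loss will provide at least 80% power to detect an overall difference between groups". For the overall F test with 2 and 402 df, λ = n Σ(μᵢ − μ̄)² / SD².
- 0/2/4: λ = 135 × (4 + 0 + 4)/100 = 10.8. Power is 76.6% at 0.025 and 84.3% at 0.05.
- 0/4/4: λ = 135 × (64/9 + 16/9 + 16/9)/100 = 14.4. Power is 88.9% at 0.025 and 93.3% at 0.05.

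The stated 80% is met for 0/4/4 but not for 0/2/4, the least favourable pattern for a 4-point range. It would be met there with no loss (n = 150, 81.6%). That is a separate matter. Here these figures are only the Bonferroni baseline.

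**Step 2. Holm by hand, independent components, same effect on both.** Let b be the power at 0.025 and a the power at 0.05.
- Per component: b + (a − b)b
- Both: b² + 2b(a − b)
- At least one: 1 − (1 − b)², the same under both rules

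0/2/4: per component 0.766 + 0.077 × 0.766 = 0.825. Both: 0.587 under Bonferroni and 0.587 + 2 × 0.766 × 0.077 = 0.705 under Holm.

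0/4/4: per component 0.889 + 0.044 × 0.889 = 0.928. Both: 0.790 under Bonferroni and 0.790 + 2 × 0.889 × 0.044 = 0.868 under Holm.

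Because the chance of at least one is unchanged, the gain per component is always half the gain for both.

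**Step 3. With correlation** (simulation, 400,000 replicates per setting, Bonferroni to Holm)

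| Pattern on both components | ρ | Per component | Both |
|---|---|---|---|
| 0/2/4 | −0.3 | 76.6% to 83.1% | 56.3% to 69.3% |
| 0/2/4 | 0 | 76.6% to 82.4% | 58.6% to 70.3% |
| 0/2/4 | 0.5 | 76.6% to 81.6% | 64.0% to 73.8% |
| 0/2/4 | 0.9 | 76.6% to 80.1% | 70.9% to 78.0% |
| 0/4/4 | −0.3 | 88.8% to 93.0% | 78.1% to 86.5% |
| 0/4/4 | 0.9 | 88.9% to 91.2% | 85.4% to 90.0% |

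The gain is 3.6 to 6.5 points per component and 7.1 to 13.0 for both under 0/2/4. Under 0/4/4 it is 2.3 to 4.2 and 4.5 to 8.4.

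**Step 4. Where there is no gain.** If only one component has the 0/2/4 effect, its gain at ρ = 0 is (0.843 − 0.766) × 0.025 = 0.002, or about 0.2 points. For at least one component the gain is zero.

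**Step 5. Error of the two overall tests.** With both nulls true, the chance of any rejection is 4.98% under either rule at ρ = 0, and 4.7% at ρ = 0.5. With one component null, Holm rejects it falsely 4.4% of the time (Bonferroni 2.5%), still below 5%.

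**Step 6. Error once follow-ups count.** Suppose PCS is affected in one SMBG arm only and MCS is null. If the PCS follow-ups keep 0.025 while MCS moves to 0.05, the limiting chance of any false HRQOL claim with independent components is 1 − 0.975 × 0.95 = 0.074. Under Bonferroni it is 1 − 0.975 × 0.975 = 0.049.

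**Step 7. A gated version.** MCS moves to 0.05 only after the PCS overall test and all PCS follow-ups are rejected at 0.025, and vice versa. In simulation at ρ = 0, without the contrast, the familywise error matched Bonferroni's in every setting run. Power for both components rose from 59% to 63% under 0/2/4 and from 79% to 86% under 0/4/4. It hardly moved when only one arm had an effect.

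**The case against.** Bonferroni is valid and prespecified. The two sections agree on it, the power calculation matches it, and it comes with simple simultaneous intervals. The article nowhere sets showing both components as an objective, and the chance of finding some HRQOL effect is the same under either rule. All of this stands, and it limits the point to one of efficiency.

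A reader might infer that the trial discards power whatever the truth. The documents do not support that. They do not say that SMBG is expected to move both components, and without an effect on both the gain is negligible.

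A reader might also infer that changing to Holm costs nothing in error control. That is true for the two overall tests. It fails if the follow-ups are in the same family and each component's follow-ups simply run at the level at which its overall test was rejected, because the error can then reach about 7.4%. An effect in one arm only is a natural scenario here, since the two SMBG arms differ in feedback. This objection defeats that follow-up rule. It does not defeat Holm on the overall tests, or the gated version.

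**Conclusion.** The point holds as a minor one. For the two overall SF-36 tests, the fixed split is dominated by a rule with the same familywise guarantee at 0.05. If both components carry a 4-point range, the avoidable loss is about 2 to 6 points of power per component and about 5 to 13 points for showing both. These sizes rest on the plan's SD of 10, on 135 analysed per arm, and on assumptions about the middle arm and the PCS–MCS correlation. If follow-ups must share the protection, the gated version still never rejects less than Bonferroni, but its gain is smaller: about 4 points (0/2/4) to 7 points (0/4/4) for both components, and almost none for a one-arm effect. The plan contains no error on this point, and its conclusions under Bonferroni would be valid.

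**What to change.** Before unblinding, replace the Bonferroni sentence in the analysis section, and its counterpart under Sample Size, with Holm for the two overall tests, and state the family. Either of these would do:

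- *Overall tests only.* The overall three-group tests of PCS and MCS form the family. The smaller p-value is tested at 0.025 and, if significant, the larger at 0.05. Familywise control is claimed for these two tests; pairwise and contrast results are follow-up outside that control.
- *Follow-ups included.* A component moves from 0.025 to 0.05 only after the other component's overall test and all its follow-up comparisons have been rejected at 0.025.

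The second option was simulated without the contrast, so the contrast should be added and the error rechecked before adoption.

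The power calculation at 0.025 can remain as the conservative case. No patients or data are added. The cost is a dated amendment to a primary-outcome rule: the article says the analysis plan was finalized before enrolment began, and all 450 patients are now recruited. The biostatistician and principal investigators are described as blinded, so the change can still be made without knowledge of the results by arm. Holm has no simple matching simultaneous intervals, so show 97.5% intervals for both scores.
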